#### Face-to-Face Acceptation and Commitment Therapy Group + App

The multimodal ACT (ACT + app) follows the same principles described above, and addresses the same key content, but combines face-to-face sessions with non-face-to-face activities and resources, using a mobile application in order to facilitate access, patient adherence and follow-up. The participants randomly assigned to this group will receive the same intervention program as the face-to-face group described before, with the same characteristics, along with interspersed non-face-to-face activities, which will serve as support for each of the sessions. The non-contact activities will consist of metaphors used in ACT programs (i.e., Dirty glass metaphor/Man in the hole metaphor/The unwelcome party guest metaphor), mindfulness and breathing exercises using audio files, and registration of values. These activities will be delivered weekly using a mobile phone application developed by the authors for this research.

#### Waitlist Group

This group will receive the usual care during the essay, but the participants in this group will be offered to receive the face-to-face- ACT group intervention + app once the ACT groups finish the planned intervention and after post-treatment assessment.

Any participant in the intervention groups who meets any of the following criteria will be excluded: Participants’ request to left the study/Participants who stop cancer treatment or change their stage to stage IV/Difficulty to continue with the intervention due to the presence of cancer treatment associated symptoms. Participants who receive other psychological treatment during the trial will be excluded, as stated in exclusion criteria.

During the intervention sessions, the therapist will emphasize the need to attend them on a regular basis and carry out assignments, in addition to highlighting the need to attend the different assessment sessions. For the participants in the ACT face-to-face + app group, the activities to be carried out weekly using the application must be marked by the participants themselves once they are finished, so that the therapist can verify that the activity has indeed been carried out in the established period.

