### Eligibility Criteria

The inclusion criteria for participants are: Men and women, aged between 18 and 70 years/Cancer diagnosis, stages I–III/Cancer type: Breast/Lung/Colorectal/Eligible for or currently receiving cancer treatment/Ability to be fluent in Spanish/Have a smartphone with daily internet access and basic smartphone skills/app handling skills/Not currently participating in another clinical trial/Not currently receiving other psychological treatment.

The exclusion criteria for participants in the trial are: Men and women aged > 70 years/Diagnosis of cancer, stage IV or other types of cancer/Not eligible for treatment/Inability to handle himself fluently in Spanish/Not having a smartphone with daily internet access and/or lack of basic smartphone skills/app handling skills/Currently participating in another clinical trial/Currently receiving other psychological treatment.

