### Statistical Methods

Data will be analyzed following the intention to treat (ITT) and per protocol approaches. First, ANOVA or chi-square will be performed to compare the sociodemographic variables and the outcome measures at baseline (T0). Second, to examine the longitudinal changes over time (baseline, post-treatment and follow-ups) and the differences between groups in the variables under study, we will use mixed linear models, since these models are more precise than the repeated measures ANOVA (Gueorguieva and Krystal, 2004). In ITT analysis (all randomized patients are included in the analysis), incomplete or missing data will be considered using the maximum likelihood estimation method. In addition, the effect sizes will be calculated by Cohen’s *d* (bias corrected) (Hedges, 1981) as a measure of the differences between the Standardized Mean Changes (SMC) (T0-T1; T0-T2; T0-T3) of the respective groups (Becker, 1988). We will use the formula *d* = *c* ⋅ ([*M*_*pre*_ –*M*_*post*_]/*SD*_*pre*_) to obtain the SMC, where *c* is the bias correction factor, *M*_*pre*_ and *M*_*post*_ are the means of the pre–test and post–test scores, respectively, and *SD*_*pre*_ is the pre–test standard deviation score (Morris and DeShon, 2002). The SMC will be calculated for each group, providing the *d* index of the general effect size from the differences between them (Face-to-face ACT group vs. Face-to-face ACT group + App; Face-to-face ACT group vs. Waitlist group; Face-to-face ACT group + App vs. Waitlist group). Once the analyses have been performed, summary tables will be displayed for all the planned evaluations: pre-treatment (T0), post-treatment (T1), follow-up at 3 months (T2) and follow-up at 6 months (T3). The results will show frequencies and descriptive statistics (the mean, standard deviation and percentages) to summarize the characteristics of both the total sample and the participants that make up each of the three groups. Finally, the results of the study will be shown in accordance with the 2010 statement of the Consolidated Standards of Reporting Trials (CONSORT) (Moher et al., 2010; Schulz et al., 2010).

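### Exclusion after randomisation is written for the intervention groups only, without continued assessment, and on its plain reading conflicts with the intention-to-treat set of all randomised patients

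*Protocol article*

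**What the plan says.** The last part of the Waitlist Group section (protocol article, Interventions) sets a rule for what happens after randomisation: "Any participant in the intervention groups who meets any of the following criteria will be excluded". The criteria are a request to leave the study, "Participants who stop cancer treatment or change their stage to stage IV", and "Difficulty to continue with the intervention due to the presence of cancer treatment associated symptoms". A further sentence is not limited by arm: "Participants who receive other psychological treatment during the trial will be excluded, as stated in exclusion criteria".

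Statistical Methods says "Data will be analyzed following the intention to treat (ITT) and per protocol approaches". It defines the first of these in brackets, "In ITT analysis (all randomized patients are included in the analysis", and adds that "incomplete or missing data will be considered using the maximum likelihood estimation method".

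Eligibility Criteria admits patients who are "Eligible for or currently receiving cancer treatment". Assessments are at T0, at the end of the 8-week intervention (T1), and 3 and 6 months later (T2, T3). The article does not say whether an excluded participant stops sessions, stops assessments, or leaves the analysis.

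**The concern.** Stopping cancer treatment and progressing to stage IV can happen in any of the three arms, yet the rule acts on them in two arms only. The symptom criterion is tied to attending the intervention, so it cannot operate on waitlist before T1. If excluded means leaving the trial, randomised groups that were comparable at T0 are thinned after randomisation in the ACT arms and left whole on waitlist, for reasons linked to health.

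At stake are hypotheses 2 and 3 (each ACT arm against waitlist) for psychological flexibility and for the secondary outcomes. Several of these, such as fatigue, insomnia and quality of life, may respond directly to progression or to treatment symptoms. The wording on stopping cancer treatment adds to the problem. Many participants will be on treatment at entry and are followed for 8 weeks plus 6 months, and the text does not separate finishing a planned course from abandoning it. A later analysis plan cannot recover questionnaires that were never collected.

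**Working it through.** **1. The two passages side by side**

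| Question | Waitlist Group section | Statistical Methods |
|---|---|---|
| Who is affected? | Intervention groups for the listed events; all participants for other psychological treatment | All randomised patients |
| What happens? | Excluded | Included in the intention-to-treat analysis |
| Assessed afterwards? | Not stated | Not stated; incomplete data go to maximum likelihood |

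Two details suggest that excluded means leaving the trial. The first listed item is a request to leave the study itself. The sentence on other psychological treatment refers back to the trial's exclusion criteria, and stage IV is one of those criteria.

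**2. The plan's own yardstick**

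From Sample Size: f = 0.25 (d = 0.5), power 0.80, alpha 0.05, correlation 0.5, 102 participants. With three groups and four occasions, the between-groups repeated-measures test has noncentrality f² × N × 4 / (1 + 3 × 0.5) = 0.0625 × 102 × 4 / 2.5 = 10.2 on (2, 99) degrees of freedom. Power is 0.811, and N = 99 gives 0.798. The stated 102 reproduces, so d = 0.5 is a fair scale for judging a bias.

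**3. Size of a one-sided exclusion (illustration)**

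The document gives no exclusion rate and no prognosis for those excluded, so both inputs are assumed. Let q be the share of an ACT arm removed, and D the number of SDs by which they would have scored worse than those kept. The full-arm mean differs from the retained mean by q × D, and that is the bias.

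- q = 0.10, D = 0.5: 0.10 × 0.5 = 0.05 SD; 0.05 / 0.5 = 10% of the planned effect.
- q = 0.20, D = 0.8: 0.20 × 0.8 = 0.16 SD; 0.16 / 0.5 = 32%.

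If waitlist also loses participants, the net bias in favour of ACT is q(ACT) × D(ACT) − q(waitlist) × D(waitlist). It is zero when the two products are equal and reverses when the second is larger.

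**4. Does adjustment for T0 remove it?**

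Simulation: 38 per arm, no true effect, T0-T1 correlation 0.5, T0 in the model, 6,000 runs. The event arises after T0, is unrelated to the T0 score, and worsens T1 by D in both arms. Those with the event are dropped from ACT only.

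| q | D | Spurious benefit (SD) | Two-sided type I error |
|---|---|---|---|
| 10% | 0.5 | 0.049 | 0.056 |
| 10% | 1.0 | 0.099 | 0.071 |
| 20% | 0.5 | 0.102 | 0.074 |
| 20% | 1.0 | 0.197 | 0.137 |

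With everyone kept, bias was about 0 and type I error about 0.05. The simulation error on a rate of 0.05 is √(0.05 × 0.95 / 6000) = 0.003, so the first row is barely distinguishable from nominal.

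The opposite case also matters. When removal in ACT depends only on the T0 score (10-20% removed), completers differ by 0.035-0.071 SD but the likelihood estimate is about zero. A rule that differs by arm is therefore not harmful in itself. Harm needs an event that carries information about T1 beyond arm and T0.

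**The case against.** The strongest reply is that the rule sits under Interventions, names the intervention groups, and includes trouble continuing with the intervention. It may therefore describe only the end of the allocated sessions, with these events feeding the per-protocol set while the intention-to-treat set keeps everyone. That reading is possible, and it would remove the conflict. It does not fit well with the request to leave the study or the reference to the exclusion criteria, and the article does not state it.

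Several stronger conclusions are tempting but unsupported:

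- **That the two sections can never both be followed.** If T0 data are kept, excluded participants remain formally in a likelihood-based model. The conflict is on the plain reading and is not proven.
- **That maximum likelihood fails because the loss is made by rule and differs by arm.** Arm is in the model, so such loss can be missing at random. The doubt concerns events after T0, especially before T1, when T0 is the only score to condition on. The document does not establish a link between the events and unobserved flexibility scores.
- **That the bias must favour ACT.** Exclusion for other psychological treatment may fall more on waitlist and remove its distressed members. Participants who complete cancer treatment need not be worse off. Either could pull the other way.
- **That the rule uses up the 10% dropout allowance.** That figure covers losses during intervention and evaluation and may already include these events.

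The reach is also limited. Both ACT arms share the rule, so hypothesis 1 is less affected. Waitlist is offered ACT + app after T1, so T2 and T3 contrasts with waitlist are already altered by crossover. The distinct harm is mainly at T1.

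**Conclusion.** The point holds as an arm-specific exclusion rule whose plain reading conflicts with the stated intention-to-treat definition and which leaves assessment after exclusion undefined. The resulting bias in the ACT versus waitlist contrasts is possible and probably favours ACT, but neither its presence nor its direction is demonstrated. The 0.05-0.16 SD figure rests on assumed exclusion rates and prognosis, complete loss of T1 for those excluded, no offsetting loss on waitlist, and an event not explained by T0. It shows what could happen and is not an estimate for this trial. It should be fixed, because the correction is cheap and the lost assessments cannot be recovered. The evidence does not support treating the contrasts as already invalid.

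**What to change.** Reconcile the Waitlist Group section with Statistical Methods:

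- State what excluded means. Participants with these events, in any arm, remain in the trial, are assessed at T1-T3 unless they withdraw consent, and are analysed as randomised in the intention-to-treat analysis. The same applies to those who take up other psychological treatment.
- Record the events in the same way in all three arms.
- Use them only to define the per-protocol set, with criteria that apply equally to waitlist wherever they can.
- State whether stopping cancer treatment includes completing a planned course.

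Whether any of these events ends the study intervention is for the investigators to decide, and no rule is proposed here. The cost is a wording change, a few more questionnaires, and possibly a smaller estimated effect, since participants who did not complete the intervention stay in the analysis. Withdrawals of consent will still leave some missing data, so bias is reduced but not abolished.

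### Prognosis-related exclusions after randomisation are written for the ACT arms only and conflict with the ITT definition; if assessment stops at exclusion, the ACT-versus-waitlist contrasts can be biased

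*Protocol article*

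**What the plan says.** Under Waitlist Group, the protocol article gives a rule for leaving the trial after randomisation: "Any participant in the intervention groups who meets any of the following criteria will be excluded". Apart from the participant's own request, which is not at issue here, the list contains "Participants who stop cancer treatment or change their stage to stage IV" and "Difficulty to continue with the intervention due to the presence of cancer treatment associated symptoms". The next sentence has no arm limit: "Participants who receive other psychological treatment during the trial will be excluded, as stated in exclusion criteria".

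Statistical Methods says: "Data will be analyzed following the intention to treat (ITT) and per protocol approaches". It then defines the first of these: "In ITT analysis (all randomized patients are included in the analysis), incomplete or missing data will be considered using the maximum likelihood estimation method".

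The article does not say whether an excluded participant leaves the sessions, the T1-T3 assessments or the analysis, or whether outcomes are still collected afterwards.

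**The concern.** The three clinical events arise after randomisation and can be expected to go with worse scores. A rule that takes such patients out of two arms and not the third breaks the comparability that randomisation gave. The symptom criterion is the most exposed, because fatigue, insomnia and quality of life are secondary outcomes and cancer-treatment symptoms bear on all three.

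If exclusion also ends assessment, the ACT arms are measured at T1 without their most symptomatic or progressing patients, while comparable waitlist patients may still be measured. ACT could then look better than waitlist with no treatment effect. Questionnaires that were never given cannot be recovered by any later analysis plan, so this has to be settled in the protocol.

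**Working it through.** **Scope of the rule.**
- The list names the intervention groups; the following sentence, on other psychological treatment, names no arm. The Sample Size section also sets the interventions against the waitlist group. Both support an ACT-only reading.
- Against this, Study Design and Settings lists the waitlist among the three interventions, and the rule stands under the Waitlist heading. ACT-only is the natural reading but not a certain one.
- The symptom criterion is asymmetric on either reading, because waitlist patients have no sessions to continue before T1.

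**Conflict.** One section excludes these participants and the other includes everyone randomised. Both can stand only if exclusion means leaving the sessions or the per-protocol set. The article does not say so.

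**Plan's own figure.** The repeated-measures ANOVA, between-groups test, has noncentrality f² × N × m / (1 + (m − 1)ρ). With f = 0.25, N = 102, m = 4 and ρ = 0.5 this is 0.0625 × 102 × 4 / 2.5 = 10.2, giving power 0.811. The stated 102 is reproduced and is not affected by this point. From this section I take 38 per arm and ρ = 0.5.

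**Size of the bias at T1.** The documents give no exclusion rate and no correlation between the events and the outcomes, so both are assumptions. Assume no treatment effect, the worst fraction p of an ACT arm by symptom burden unmeasured at T1, symptom burden correlated r with the T1 outcome, and the waitlist fully measured.
- Unadjusted bias = r × φ(z)/(1 − p), where z is the upper-p point of the standard normal.
- Adjusted for T0, with burden linked to T0 only through the T1 outcome: bias = (1 − ρ²) × r × φ(z)/(1 − p), with 1 − ρ² = 0.75.
- φ(z)/(1 − p) is 0.109 for p = 5%, 0.195 for 10% and 0.350 for 20%.

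| Excluded | r | Adjusted bias (SD) | Simulated error rate |
|---|---|---|---|
| 5% | 0.3 | 0.75 × 0.3 × 0.109 = 0.02 | about 5% |
| 10% | 0.3 | 0.75 × 0.3 × 0.195 = 0.04 | about 5% |
| 10% | 0.5 | 0.75 × 0.5 × 0.195 = 0.07 | 6-7% |
| 10% | 0.8 | 0.75 × 0.8 × 0.195 = 0.12 | about 9% |
| 20% | 0.5 | 0.75 × 0.5 × 0.350 = 0.13 | about 9% |
| 20% | 0.8 | 0.75 × 0.8 × 0.350 = 0.21 | 17-19% |

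Error rates are from simulations of 6,000 runs per cell, 38 per arm, ANCOVA on T0, nominal 5% two-sided. The simulated biases agree with the formula to within about 0.01 SD.

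**A simpler model.** Suppose a share p of each arm has an event, these patients score D SD worse at T1, and their T1 scores are missing in ACT only. The bias is p × D: from 0.05 × 0.3 = 0.015 to 0.20 × 0.8 = 0.16 SD. A likelihood-type analysis adjusted for T0 gave 0.01 to 0.16 SD in simulation, so adjustment removed almost nothing when T0 did not predict the event.

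**Direction.** Losing symptomatic or stage IV patients from ACT probably favours ACT. Stopping cancer treatment is different. Patients enter as "Eligible for or currently receiving cancer treatment", and T3 falls about 8 + 26 = 34 weeks after the start of the sessions. Read literally, the criterion also covers planned completion of treatment, and losing those patients could work against ACT.

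**Time point.** After the T1 assessment the waitlist is offered ACT + app. T2 and T3 are therefore no longer comparisons with an untreated group, and the figures above apply to T1.

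**The case against.** The strongest defence is that the list sits under Interventions, just before the paragraph on attendance and assignments, and can be read as ending the sessions only. Excluded patients would then leave the per-protocol set, while the ITT analysis keeps everyone randomised with whatever data they have. This has force. A reader might infer that the ITT analysis does not hold; the article does not support that, since Statistical Methods expressly keeps all randomised patients. What remains is that the article never says assessment continues. Where it does not, most of these patients contribute T0 only, and the ITT result rests on a missing-at-random assumption that unobserved worsening would violate. Dependence of missingness on arm alone would do no harm with arm in the model. The per-protocol analysis is no safeguard, because it drops the same patients.

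Other stronger inferences also fail:
- **A fully unselected waitlist.** The exclusion for other psychological treatment and the freedom to withdraw apply to every arm, and the article nowhere states that waitlist patients with these events are assessed.
- **Bias in Hypothesis 1.** Both ACT arms share the rule and the same face-to-face programme. The app is offered "in order to facilitate access, patient adherence and follow-up", but adherence is not a listed outcome, and nothing says the app was added for symptomatic patients.
- **A retention shortfall.** One could compute 38 × 0.9 × 0.9 = 30.8 or 38 × 0.9 × 0.8 = 27.4 against the required 34. The 10% dropout allowance may already cover these losses, so that would double count.
- **Bias as a share of the planned d = 0.5.** That effect is for psychological flexibility, whereas the selection argument is strongest for the symptom scales. The documents do not support a high correlation between treatment symptoms and the AAQ-II.

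**Conclusion.** The point holds as a contradiction between two stated rules, with a risk of bias that depends on how exclusion is applied. The exclusions are ACT-only on the natural reading, the symptom criterion is asymmetric on any reading, and the article does not reconcile them with an ITT analysis of all randomised patients.

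If assessment stops at exclusion, the ACT-versus-waitlist contrasts at T1 can be biased, probably towards ACT for the symptom and stage IV criteria and in an unclear direction for stopping treatment. Maximum likelihood does not cure this when the event reflects worsening that observed scores miss. With 5-10% excluded and a weak correlation (r = 0.3), the bias is about 0.02-0.04 SD and the error rate stays near 5%. With 20% excluded and r = 0.8, it is about 0.2 SD with an error rate of 17-19%. Those rates and correlations are assumptions. The upper end requires many exclusions within an 8-week course in stage I-III patients. If assessment continues in all arms, this bias does not arise.

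**What to change.** Reconcile Waitlist Group with Statistical Methods:
- State that the three events may end the sessions and may define the per-protocol set, but do not end follow-up or remove a patient from the ITT analysis. Whether a patient continues sessions remains a clinical decision, left as it is.
- Ask patients with these events in all three arms to complete T1-T3 unless they withdraw consent.
- Record the events, with dates, in the same way in every arm.
- Analyse as randomised.
- Optionally, add a sensitivity analysis that shifts the values of patients with missing data after such an event towards worse scores.

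The separate exclusion for other psychological treatment is not part of this change. The cost is revised wording, an ethics notification and questionnaires for a few more patients. The estimated benefit of ACT may come out smaller.

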### Outcomes

#### Primary Outcomes

Taking into account the data obtained by previous research in similar studies, it is expected to observe a significant increase in the mean of the scores obtained in psychological flexibility evaluated with the acceptance and action questionnaire-II (AAQ-II) questionnaire in patients who receive the combined intervention face-to-face ACT + app when comparing the scores obtained in T0 (pre-treatment) with T1 (post-treatment). It is also expected that the scores obtained will remain stable in the two follow-up assessment points, T2 (3 months after completion of the intervention) and T3 (6 months after). Also, it is expected that the mean scores in psychological flexibility will be statistically significant higher in the face-to-face ACT + app group than in the face-to face ACT group at the different assessment points. In addition, it is expected to observe significant improvements in psychological flexibility in the group that receives the face-to-face ACT + app intervention compared to the waitlist group at T1, T2, and T3. Finally, it is expected to observe a significant difference in psychological flexibility in the face-to-face ACT group compared to the waitlist group at the aforementioned evaluation moments.

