1.The combined intervention (face-to-face ACT + app) will be more effective in increasing psychological flexibility, quality of life and post-traumatic growth and reducing symptoms of anxiety, depression, fatigue and insomnia than the face-to-face ACT intervention at posttreatment and at the two follow-up periods (3 and 6 months).2.The face-to-face ACT + app group will achieve significant improvements in psychological flexibility, quality of life and post-traumatic growth and significant reductions in anxiety, depression, fatigue, and insomnia compared to the waitlist group after the intervention and at the two follow-up periods (3 and 6 months).3.The face-to-face ACT intervention group will significantly increase psychological flexibility, quality of life and post-traumatic growth, and reduce symptoms of anxiety, depression, fatigue, and insomnia compared to the waitlist group after the intervention and at the two follow-up periods (3 and 6 months).

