### Sample Size

To determine the optimal sample size, we considered the effect sizes in psychological flexibility obtained in previous works by other authors. A recent meta-analysis (Chunxiao et al., 2020) examined the effect of ACT (including face-to-face and internet-based modalities) on psychological flexibility compared with treatment as usual or waitlist in cancer patients. The results showed a moderate effect size (Hedges’ *g*) of 0.58 at post-treatment. Taking into account these results, a medium effect size of 0.5 (Cohen’s *d*) has been assumed to detect differences between the interventions and waitlist group. Since no software to determine sample size for linear mixed model analyses was available, we used the *f* index of G*Power. Therefore, an effect size of 0.25 (index f) is assumed, equivalent to Cohen’s *d* = 0.5. Thus, with a statistical power of 0.80, an alpha level of 0.05 and a correlation between repeated measures of 0.5, a total sample of 102 participants is required (34 subjects in each group). In order to control the lack of participants during the intervention and evaluation process, based on a previous study (Arch and Mitchell, 2016) we assume a dropout rate of 10%. Consequently, we require to include 112 participants in our study (38 participants per group).

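### The primary outcome mixes an uncontrolled pre-post change, undefined stability and three between-arm contrasts at three visits, and does not say which contrast and visit decides the trial

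*Protocol article*

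**What the plan says.** Under Primary Outcomes, the protocol article sets out a series of results it expects on the AAQ-II:

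- a significant T0-T1 change within one arm, "in patients who receive the combined intervention face-to-face ACT + app when comparing the scores obtained in T0 (pre-treatment) with T1 (post-treatment");
- maintenance of that change: "It is also expected that the scores obtained will remain stable in the two follow-up assessment points", with no margin and no method of judging it;
- ACT + app better than ACT alone at the assessment points;
- ACT + app better than waitlist at T1, T2 and T3;
- ACT different from waitlist at the same visits.

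The three numbered hypotheses in the Introduction repeat the three contrasts at all three visits. The first, for example, expects the combined arm to do better "than the face-to-face ACT intervention at posttreatment and at the two follow-up periods (3 and 6 months"). The objectives are partly ranked: first the combined arm against both others, second ACT against waitlist.

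The only significance level is in Sample Size: "an alpha level of 0.05 and a correlation between repeated measures of 0.5". Statistical Methods names mixed linear models and plans effect sizes for all three contrasts over all three intervals. It does not single out one of them.

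Under Waitlist Group, that arm is offered ACT + app after the post-treatment assessment. The Discussion says this treatment starts immediately after the two ACT groups finish, and acknowledges that this may limit information on long-term effects.

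**The concern.** A primary outcome should tell the reader in advance which result decides the trial. This one does not, and three of its parts are weak in themselves.

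1. **The pre-post criterion.** A change within one arm mixes the effect of treatment with natural course and regression to the mean. In a three-arm randomised superiority trial, it can be met when the intervention does nothing.
2. **Stability.** Without a margin, nothing defines when a gain counts as maintained. A non-significant change in an arm of 34 would not show it.
3. **The waitlist at T2 and T3.** Four of the nine between-arm comparisons (two waitlist contrasts at two visits) set an ACT arm against patients who have been offered treatment. The intervention lasts 8 weeks and starts right after T1, so it can be finished before T2 at 3 months. These comparisons set immediate treatment against a delayed offer and no longer measure the effect against an untreated control.

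With no deciding contrast or visit, a positive conclusion could also be built on whichever listed comparison turns out significant.

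**Working it through.** **Inputs from Sample Size.** "with a statistical power of 0.80"; alpha 0.05 (two-sided assumed, as sidedness is not stated); "an effect size of 0.25 (index f) is assumed"; "a correlation between repeated measures of 0.5"; 34 per arm, 102 in total. Study Design gives three arms and four assessments.

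**Step 1: the plan's own figure.** For a repeated-measures between-groups F test, λ = f²·N·m / [1 + (m − 1)ρ] = 0.0625 × 102 × 4 / 2.5 = 10.2. With 2 and 99 degrees of freedom the power is 0.811, and 102 is the smallest multiple of 3 that reaches 0.80. The within-subject version gives 24 and the interaction version 30. So 102 matches an overall three-group test averaged over four visits, which is none of the comparisons listed as primary.

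**Step 2: the pre-post criterion with no treatment effect.** The SD of change is SD × √[2(1 − 0.5)] = 1 SD, so the standard error is 1/√34 = 0.171 SD. The document gives no natural drift; 0.2 to 0.3 SD in all arms is an assumption.

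| Drift | Drift × √34 | Chance of p < 0.05 (normal) | Same, t test |
|---|---|---|---|
| 0.2 SD | 1.17 | 21% | 20% |
| 0.3 SD | 1.75 | 42% | 40% |

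**Step 3: what non-significance would say about stability.** With the same standard error, an observed loss is non-significant up to about 2.03 × 0.171 = 0.35 SD. That is 0.35/0.5 = 70% of the assumed gain of d = 0.5.

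**Step 4: false positives over the listed tests.** Three contrasts at three visits make nine tests, and the pre-post test makes ten. The table comes from simulation (400,000 replicates per row, normal tests, equal correlation 0.5, no group or time effect). It supposes that each test is unadjusted at two-sided 0.05 and that any one significant result counts.

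| Scores used | Nine between-arm tests | With pre-post added |
|---|---|---|
| Raw score at each visit | 28.5% | 31.7% |
| Change from baseline | 28.6% | 30.3% |
| Baseline-adjusted | 30.6% | 32.8% |

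Over assumed correlations of 0 to 0.8, the ten-test figure runs from about 26% to 35%. Treating the tests as independent gives 1 − 0.95⁹ = 37.0% and 1 − 0.95¹⁰ = 40.1%, which is too high because the tests share patients.

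**Step 5: other readings of the same text (r = 0.5).**

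- Only results in the hypothesised direction count: 16-17% for nine tests, 17-18% for ten.
- A contrast counts only if significant at all three visits: 0.3-0.9% that any contrast qualifies.
- An overall group test across T1-T3 must be significant first: about 5%.

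**Step 6: after the fix.** Three unadjusted contrasts at T1 alone give about 12%. With an overall three-group test at T1 required first, the rate is 5%.

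**The case against.** The strongest reply is that testing each comparison at 0.05 is not stated. The figure "an alpha level of 0.05" stands only in the sample-size calculation. An adjustment or an overall test first is what an article commonly leaves to the analysis plan, which is not shown. The section is also worded as expectations, and nothing says that one significant result out of ten would be success. This stands. A reader might infer that the trial runs a false-positive risk of 31-33%, but the document does not support that: it is the upper case among the readings in Steps 4 and 5.

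A reader might also infer that the comparisons have no order at all. The Introduction's ranking of the objectives shows otherwise, although it leaves two contrasts together in first place and names no visit.

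Nor should the pre-post sentence be taken as the trial's main criterion because it comes first. All three hypotheses are between-arm, and the sentence adds only about 2-3 percentage points to the error rate when there is no drift. It is nevertheless stated as a primary outcome, and Step 2 shows what it does if scores drift.

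Finally, no passage says that stability will be concluded from a non-significant change, and standardised mean changes are planned for every interval. So the point on stability is the missing margin, not a wrong test.

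None of this touches the core. What the primary outcome is belongs to the protocol, and this one states it without a deciding contrast or visit.

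**Conclusion.** The point holds as a badly fixed primary outcome. Three parts rest on the text alone: no deciding contrast and visit, a pre-post criterion that ignores randomisation, and waitlist contrasts at T2 and T3 after that arm is offered treatment.

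The sizes are conditional. The 21-42% for the pre-post criterion assumes a natural drift of 0.2-0.3 SD, n = 34 and r = 0.5. The 28-31% for nine tests (30-33% for ten) assumes unadjusted two-sided 0.05, no effect anywhere, and success on any one result. The article neither states nor excludes those conditions, and under stricter readings the figure falls to 16-18% or below 1%. The lack of a stated multiplicity method is not itself the finding.

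The outcome definition should be changed, and the change is cheap.

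**What to change.** - Define the primary endpoint as the between-arm difference in AAQ-II at T1, estimated from the planned mixed model. The waitlist is still untreated at that visit.
- Control the three contrasts at 5% overall by a procedure stated in advance. One option is an overall three-group test at T1 followed by pairwise tests. Another is a fixed sequence, with the order justified against the ranking of objectives in the Introduction. The choice is the sponsor's.
- Make T2 and T3 secondary, and confine the randomised comparison there to the two ACT arms.
- Report within-arm change, and maintenance from T1 to T3, only as estimates with 95% CIs.

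The change is to wording in the outcome and analysis sections; it adds no patients or visits. Fewer results can be claimed as primary, and under a fixed sequence a later contrast cannot be claimed once an earlier one fails. That could happen often: with 34 per arm and d = 0.5, one pairwise test at T1 has about 54% power, or 66% if baseline-adjusted at r = 0.5. The 80% in Sample Size belongs to the averaged overall test, so the power for the chosen primary comparison should be restated.
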